### Measurements

The assessments will be conducted by a researcher blinded to the randomization, trained in using the instruments. CDRs will be assessed by a psychiatrist and a trained CDR rater blinded to the randomization. Self-rated scales will be completed by the participants under guidance.Screening Instrument:1.1*The CDR* is a semi-structured interview with six dimensions: memory, orientation, judgment, community affairs, hobbies and habits and personal care. Each item from its corresponding dimension will then be converted to an average score for that dimension. The average score for each dimension will be converted to a defined range and a combination of those ranges will produce an overall CDR rating ranging from 0 to 5 [34]. In the selection of very mild to mild grade dementia, participants with scores from 0.5 (and 0.5 or more on 3 or more domains) to 1 will be selected in accordance with previous studies [7]. The CDR will be assessed before randomization and at the final 12-month follow up.Psychosocial Assessments:2.1*The Chinese Neuropsychiatric Inventory (NPI)* assesses 12 psychological and behavioral symptoms of patients with neurodegenerative disorders. Categorized as behavioral problems (agitation/aggressiveness, disinhibition, irritability, aberrant motor behavior), psychosis (delusions and hallucinations), mood disturbance (depression, anxiety, sleep, appetite, apathy) and euphoria. This tool will be administered by a trained research assistant to their main caregivers based on informant ratings [35].2.2*The Abbreviated Chinese Geriatric Depression Scale (ac-GDS)* is a 4-item version selected to provide a simple and reliable assessment of depressive mood in elderly dementia patients. With depression being one of the most common concomitants of dementia, participants’ subjective well-being can be profoundly affected. The GDS is self-rated by the participants [36].2.3*The Chinese de Jong Fierveld Loneliness Scale (c-JFLS)* is a 6-item self-reported scale based on a 3-point scale. The items are associated with feelings of being alone, rejection and a sense of having support [37]. The scores are associated with social variables related to contact with family, relatives and close persons, or just having people around.2.4*The Visual Analogue Mood Scale (VAMS)* is a reliable and sensitive single-item assessment of 8 affective states: afraid, confused, sad, angry, energetic, tired, happy and tense [38]. It was designed to offer a simple and direct means of assessing various mood states in neurologically impaired adults. On a visual analogue scale of 0 to 100, the respondents are asked to rate the intensity of their mood. The presence of positive mood markers is also a hallmark of this scale.Cognitive Functioning:Cognitive functioning tests will be assessed by a trained research assistant.*The Digit Span Test* is an indicator of cognitive impairment in dementia to assess executive functioning. The tasks require immediate memory of numbers and the maintenance and manipulation of information in the mind. This test has good validity for elderly participants in Hong Kong [39].*Fuld Object Memory Evaluation* measures episodic memory, which is a profound area of loss in dementia. The tasks require the remembering of ten unrelated items over five immediate recall trials and a delayed recall trial. This evaluation makes use of multiple sensory systems, not just auditory or visual cues, and is thus more pertinent to what is being promoted through dance movement. The Chinese version has been validated [40].*The Trail Making Test (Parts A and B)* measures visuospatial construction as the participant draws lines between alternate numbers, which requires visual search, attention and mental flexibility. Chinese norms for the scale have been established [41].Functioning Assessments4.1*The Lawton Instrumental Activities of Daily Living -Hong Kong version (IADL-hk)* is an 8-item, self-reported measure of community living and functioning skills [42]. Daily functional skills including cooking, use of the telephone, use of transport, household management, money management and shopping skills, measured on a scale of 0 to 8.Biomarker5.1Salivary cortisol collection will be conducted using the “Salivette” collection device, which includes a cotton swab placed under the tongue by the participants, with the assistance of a daycare nurse. Saliva samples will be collected at 5 prescribed times (awakening, 45 min post-awakening, 12:00, 5:00 and 9:00 pm) and kept frozen at −20 °C. Smoking, eating and drinking is not allowed 1 h before saliva collection.5.2Daily condition measures of the participants’ health behavior and activities on the day of saliva collection will be collected along with cortisol readings. Self-rated on a scale of 1 to 10, these conditions include (i) sleep quantity that day (hours of sleep at night and nap hours), (ii) subjective sleep quality rated on a scale of 1 to 10, (iii) smoking habit and the number of cigarettes consumed that day, (iv) alcohol/coffee drinking habit and the approximate intake amount that day and (v) subjective evaluation of stress level on the day of collection. All of the above measures will affect the diurnal cortisol rhythm and must be considered in data interpretation.Socio-demographic and Clinical Information6.1The patients’ socio-demographic and clinical information will be solicited. Socio-demographic data will include age, gender, education level and marital status. The type, frequencies and durations of regular exercise will also be recorded. Clinical information will include the duration and severity of dementia diagnoses, symptoms, other psychiatric diagnoses, other illnesses, medications, other treatments and hospitalization during the study. Their medications and other adjunctive treatments, including psychosocial care, will also be collected to control for confounding variables when modeling outcomes.

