## Methods/Design

### Research design

This study will adopt a 3-arm RCT design with waitlist control. After screening and collecting baseline data, computer-generated random numbers will be used to randomize the eligible participants into one of three intervention groups: dance movement, exercise or waitlist control. The waitlist control group will be provided with a dance-movement or exercise intervention upon study completion. All of the participants will continue to receive regular medication and care. Four repeated assessments will be conducted for all of the participants at baseline, post intervention (3 months), and 6 and 12 months after the baseline. The manuscript and flow diagram (Fig. 1) adheres to CONSORT guidelines.

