
### Exploring the efficacy of dance-therapy intervention

An intention-to-treat analysis will be used to prevent participant selection biases attributed by study discontinuation. The efficacy of the dance-movement intervention will be compared to the exercise intervention and waitlist control using a repeated measures analysis of variance across the four assessment time points after adjusting for confounding variables. An ordinary least squares regression will be used to understand the relationships between the dependent variables (outcomes) and independent variables (covariates). To examine the interventions’ effects on prognoses and the likelihood of participants’ progressing to more severe stages of dementia, odds ratios will be conducted on CDR scores. The data analysis procedures will be conducted using SPSS and MPlus software with criteria for levels of significance set at *p* < .05.

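### Medication and adjunctive care, apparently including that given after randomisation, are to be adjusted for as confounders; arm comparisons should use pre-randomisation covariates only

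*Protocol article*

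**What the plan says.** In the Measurements section, the item on socio-demographic and clinical information (6.1) ends its list of clinical data with "other illnesses, medications, other treatments and hospitalization during the study". The next sentence gives the purpose: "Their medications and other adjunctive treatments, including psychosocial care, will also be collected to control for confounding variables when modeling outcomes".

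The section on exploring the efficacy of the intervention compares the three arms by "repeated measures analysis of variance across the four assessment time points after adjusting for confounding variables". It does not list those variables or say when they are measured. The same paragraph opens with "An intention-to-treat analysis will be used to prevent participant selection biases attributed by study discontinuation".

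Two other places bear on timing. Under Research design, "After screening and collecting baseline data, computer-generated random numbers will be used to randomize the eligible participants into one of three intervention groups", so pre-randomisation values exist for every participant. Under Inclusion criteria, medication must be stable for 30 days before screening. After that, usual medication and care go on in all arms, and nothing in the text excludes changes during the 12 months of follow-up.

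**The concern.** A confounder of the arm comparison must be a cause, or a proxy for a cause, of both allocation and outcome. Allocation here is random and follows the baseline assessment, so nothing that happens later can play that part. Treatment started or changed later can lie on the path from arm to outcome, can share causes with the outcome, or can be irrelevant.

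The first two are plausible in this trial. The outcomes include neuropsychiatric symptoms and depression, and the Background notes that antipsychotics are prescribed for behavioural and psychological symptoms, so a change in symptoms may change prescribing. Psychosocial care is close to the intervention's own proposed mechanism of social exchange and mutual support, and waitlist participants may look for it elsewhere during the year.

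What is at stake is the meaning of the main contrast. An arm effect conditioned on on-study treatment is no longer the total effect of being allocated to dance movement. It may be smaller or larger than that effect, and the trial report could not tell which.

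**Working it through.** **1. The sentences side by side.** The list in item 6.1 closes with a time qualifier. It certainly covers hospitalisation and, read naturally, also the two treatment items just before it. The following sentence takes up medications and adjunctive treatments and assigns them to confounder control in outcome models. The efficacy section then adjusts the arm comparison for confounding variables. No step in this chain restricts the values to baseline.

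**2. What adjustment does.** The document gives no figures for this, so the following is an illustration with assumed coefficients. Let A be the arm (0/1), M an on-study treatment, U an unmeasured cause with variance 1, and let the residual SDs be 1:

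- M = a·A + u·U + error
- Y = d·A + b·M + u·U + error, with Y a symptom score and d the direct effect

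The total (randomised) effect is d + a·b. Given A and M, the expected value of U is [u/(1 + u²)]·(M − a·A). The coefficient of A adjusted for M is therefore d − a·s, with s = u²/(1 + u²). The difference, adjusted minus total, is −a·(b + s).

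With d = −0.30 throughout, and s = 0.25/1.25 = 0.2 when u = 0.5:

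| a | b | u | Total | Adjusted | Adjusted/total |
|---|---|---|---|---|---|
| 0 | 0.3 | 0.5 | −0.30 | −0.30 | 100 % |
| −0.3 | 0.3 | 0 | −0.39 | −0.30 | 77 % |
| −0.3 | 0 | 0.5 | −0.30 | −0.24 | 80 % |
| −0.3 | 0.3 | 0.5 | −0.39 | −0.24 | 62 % |
| −0.5 | 0.3 | 0.5 | −0.45 | −0.20 | 44 % |
| −0.3 | −0.3 | 0.5 | −0.21 | −0.24 | 114 % |
| −0.5 | −0.3 | 0.5 | −0.15 | −0.20 | 133 % |

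A simulation with one million records per row agrees to within about 0.01 in the ratio.

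**3. Reading the table.** If the arm does not change M (a = 0), adjustment does no harm. If it does, the sign of the error depends on b + s, that is, on whether M helps or harms the outcome and on how strongly it shares causes with it. The third row shows that distortion arises even when M has no effect on the outcome at all.

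**4. The plan's own figures.** The sample size does not depend on this point. With f² = 0.15, power 0.8 and a 5 % level, the overall F test of a multiple regression (noncentrality f²·N) gives N = 131 if there are 13 predictors. That number is an assumption, because the article does not state it. With 35 % attrition, 131/0.65 = 201.5, in line with the 201 stated. Neither figure changes if the covariates are taken at baseline and their number stays the same.

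**The case against.** The strongest reply is that the document never says outright that on-study values enter the arm comparison. The time qualifier may belong to hospitalisation alone, since the same list holds entry characteristics such as duration of diagnosis and other illnesses. The confounder sentence carries no time qualifier. Modelling outcomes might mean the separate ordinary least squares regression, which is meant to describe relations between outcomes and covariates. A repeated measures analysis of variance ordinarily takes covariates that are constant over time, which suits baseline values. Finally, a journal article may leave the exact covariate list to a fuller document.

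Most of this stands as a limit on certainty: the timing is not fully explicit, and baseline medication and care would be legitimate covariates. It does not remove the point. The article does more than omit a list. It states a rule that names a class of variables, calls them confounders and assigns them to outcome modelling, next to a sentence that apparently places them during the study. A single on-study summary, such as any medication change, is also constant over time, so the choice of model does not exclude it.

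Two wider readings are tempting but unsupported. A reader might infer that hospitalisation is a planned covariate; it is listed as collected, but the sentence on confounder control does not name it. A reader might also extend the point to same-day stress and sleep ratings in the cortisol analyses. The text says only "All of the above measures will affect the diurnal cortisol rhythm and must be considered in data interpretation", and the cortisol section specifies baseline correlations and an exploratory growth curve model, not an adjusted arm contrast.

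**Conclusion.** The point holds in conditional form. On its natural reading, the plan adjusts the randomised comparison for medication and adjunctive care that may have changed after randomisation, and nothing limits those covariates to baseline. If the intervention affects them, the adjusted contrast can be biased in either direction and is not the intention-to-treat effect. The intention-to-treat statement concerns participants who discontinue; keeping everyone in the analysis does not repair a contrast that conditions on later treatment.

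A reader might infer that the plan is certain to bias the result, or that a definite amount of power is lost. The documents support neither. Bias requires that the arm changes these treatments, on which the article has no data. It gives no share of the effect that runs through them and no standardised difference between arms, so no loss of power can be calculated. The 44 % to 133 % range rests wholly on assumed coefficients and shows only that the direction is open.

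The conclusion rests on two assumptions: that the time qualifier covers the treatment items, and that the confounding variables in the efficacy analysis are, at least in part, those named in item 6.1. Given both, this is a wording defect to correct before outcome data are analysed, and not a flaw in the design.

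**What to change.** Add one sentence to the efficacy analysis: covariates in all arm comparisons are limited to values measured before randomisation. Examples are the baseline value of the outcome, baseline CDR, age, education, and baseline medication and care. Amend the purpose sentence in item 6.1 to match. Report on-study medication, adjunctive care and hospitalisation by arm as descriptive results, or use them only in an analysis labelled as mediation or sensitivity.

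This needs no new data. The cost is a small amount of follow-up variance that on-study treatment might have explained.

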
### Exploring the efficacy of dance-therapy intervention

An intention-to-treat analysis will be used to prevent participant selection biases attributed by study discontinuation. The efficacy of the dance-movement intervention will be compared to the exercise intervention and waitlist control using a repeated measures analysis of variance across the four assessment time points after adjusting for confounding variables. An ordinary least squares regression will be used to understand the relationships between the dependent variables (outcomes) and independent variables (covariates). To examine the interventions’ effects on prognoses and the likelihood of participants’ progressing to more severe stages of dementia, odds ratios will be conducted on CDR scores. The data analysis procedures will be conducted using SPSS and MPlus software with criteria for levels of significance set at *p* < .05.

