### Sample size determination

A sample size of 131 has been determined. Due to the presence of multiple independent variables, multiple regression modeling with a medium effect size (f2) of 0.15, at 0.8 power and a significance level of 0.05, was used to calculate the sample size. The experimental, clinical and demographic variables anticipated to affect the intervention outcomes were included in the model. Based on prior local trials with early dementia patients, the recruitment of 201 participants is required (67 per arm), assuming an attrition rate of about 35 % [33].

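### The four-visit repeated measures ANOVA, in its conventional form, drops anyone with a missed visit, which at 35 % attrition defeats the stated aim of the intention-to-treat analysis

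*Protocol article*

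**What the plan says.** In the protocol article, the section on exploring the efficacy of the intervention opens with a principle: "An intention-to-treat analysis will be used to prevent participant selection biases attributed by study discontinuation". The next sentence names the method. Dance movement is compared with exercise and with waitlist "using a repeated measures analysis of variance across the four assessment time points after adjusting for confounding variables". The section names SPSS and MPlus as software and attaches no way of handling missing visits to this comparison. It also does not say which term of the ANOVA (arm, or arm by time) is the efficacy test.

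The schedule is fixed in the research design section, which reads "Four repeated assessments will be conducted for all of the participants at baseline, post intervention (3 months), and 6 and 12 months after the baseline". Under its sample size heading the article states "A sample size of 131 has been determined" and raises this to 201, or 67 per arm, "assuming an attrition rate of about 35" %.

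The only model named that naturally accepts incomplete records is the two-level growth curve model. It appears under the heading on cortisol and its determinants, for cortisol trajectories, and is not assigned to the efficacy comparison.

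**The concern.** A conventional repeated measures ANOVA, such as the repeated measures GLM in SPSS, needs a complete set of values at baseline, 3, 6 and 12 months. A participant who misses one visit is removed from every comparison, including those at visits attended. The two adjacent sentences therefore pull apart: the first aims to protect against bias from discontinuation, and the second names a test that by default analyses completers.

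This goes beyond an unstated detail. The article commits to a particular test that, as usually run, works against the purpose given one sentence before, in a trial that expects to lose about a third of its participants. In a progressive disease those who leave are unlikely to be a random subset. Reasons for leaving a twice-weekly group programme may also differ from reasons for leaving a 12-month waitlist. At stake are the comparability created by randomisation and the use of 3- and 6-month data that were collected.

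**Working it through.** **Inputs from the document.** Required sample 131; recruitment 201 (67 per arm); attrition about 35 %; four visits; f² = 0.15, power 0.8, significance level 0.05.

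**The plan's own figures first.**
- Overall F test in multiple regression, noncentrality f² × N: N = 131 is obtained with 13 predictors (power 0.802). Twelve give 127 and fourteen give 135. The article does not state the number of predictors, so 13 is an inference.
- Inflation: 131 / 0.65 = 201.5. The stated 201 agrees within rounding and implies 1 − 131/201 = 34.8 % attrition.

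**Who is analysed.** This takes attrition to mean not completing all four visits. Intermittent missed visits would add to the loss.
- Complete cases: 201 × 0.65 = 130.65, about 131; per arm 67 × 0.65 = 43.6.
- Randomised but excluded: 201 × 0.35 = 70.4, about 70.

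**Observed values discarded**, if the 70 leave for good:
- Values used by the ANOVA: 131 × 4 = 524.
- Values collected if all 70 leave just after baseline: 524 + 70 × 1 = 594, so 70 are discarded.
- Values collected if all 70 miss only month 12: 524 + 70 × 3 = 734, so 210 are discarded.

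**Precision at 3 months.** The document gives no timing of loss. Assume 13 % are lost by month 3. Then 67 × 0.87 = 58.3, about 58 per arm, are seen at that visit, but only 43.6 per arm enter the analysis. The ratio of standard errors is √(58 / 43.6) = 1.15, about 15 % larger. If nearly everyone who leaves has gone by month 3, the ratio approaches 1. If nobody has, it is √(67 / 43.6) = 1.24.

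**Bias, as illustration only.** All runs assume no true treatment effect and dropout that depends on the last observed score in some arms but not in others.
- 2,000 trials, 67 per arm, visit correlation 0.6, score-driven loss in one arm, completer shares 0.66 and 0.62: completer arm means differed by 0.22, 0.22, 0.23 and 0.18 SD at baseline, 3, 6 and 12 months. Subtracting the baseline gap leaves 0.00, 0.01 and −0.04 SD.
- A similar run gave 0.27, 0.27, 0.27 and 0.22 SD, which leaves 0.00, 0.00 and −0.05 SD in change from baseline.
- Very large samples, correlation 0.6, score-driven loss in two of three arms, 33 to 41 % dropout by arm: 12-month completer means were −0.16, −0.16 and −0.40 SD against a true −0.40 SD in every arm. The gap was 0.24 SD at 12 months and about 0.05 SD in change from baseline (−0.45 against −0.40).
- With correlations varied from 0.6 to 0.8, gaps ran from 0.10 to 0.29 SD, and the shift in change from baseline was at most about 0.08 SD.
- With the same dropout mechanism in every arm, arm differences were about zero.

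The spurious gap is thus mostly present at baseline among completers. It passes into the arm main effect, which averages over all four visits, and nearly cancels in the arm-by-time term.

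**The case against.** The article never mentions completers or listwise deletion; the conflict rests on how the ANOVA is conventionally run. Imputation before the ANOVA would satisfy the stated aim, MPlus can fit models to incomplete records, and a condensed article may leave missing-data handling to a fuller plan. This is right in part: a reader should not infer that the plan prescribes a completer analysis. But listing software does not choose a method, and the article ties neither imputation nor a likelihood model to the efficacy test. What remains is a named test that, in its usual form, works against the stated purpose.

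Three further objections stand:

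- A reader might infer that the treatment effect would be biased by about 0.2 SD. The simulations do not support that for change from baseline, where the shift is small. Only the arm main effect carries the gap, and the article does not say which term is the efficacy test.
- A reader might infer that the trial falls below its planned size. It does not: recruitment of 201 was set so that about 131 remain.
- Using baseline as one level of the repeated factor, tested through arm by time, is valid in a randomised trial. Baseline as a covariate is usually more efficient, but that is a preference and no error is shown.

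**Conclusion.** The concern holds in a limited form. The efficacy test named in the article, run conventionally, excludes about 70 of 201 randomised people and discards between 70 and 210 observed values, contrary to the aim stated one sentence earlier. That follows from the method and the document's own attrition figure, provided attrition means not completing all four visits. The loss of precision is relative to a method that keeps everyone; the figure of about 15 % at 3 months rests on the assumed 13 % loss by then.

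The size and direction of bias cannot be derived from the document. Under assumed score-driven dropout that differs between arms, the arm main effect is distorted by about 0.2 to 0.3 SD. Change from baseline moves by about 0.05 SD or less at correlation 0.6, and by up to about 0.08 SD when correlations up to 0.8 are tried. Dropout that depends on unobserved scores was not examined and could behave differently. A claim of serious bias in the arm-by-time test would go beyond this evidence. This should be fixed, but it does not by itself invalidate the trial.

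**What to change.** Replace the repeated measures ANOVA in the efficacy section with a likelihood-based mixed model for repeated measures on all randomised participants: arm, visit and arm by visit, with the baseline score as covariate or constrained equal across arms. Alternatively, keep the ANOVA and state that missing visits are multiply imputed first. In either case name the arm-by-visit contrasts, dance versus exercise and dance versus waitlist, as the efficacy test. A sensitivity analysis for data missing not at random is a useful option but is not needed to resolve the conflict.

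The cost is one paragraph of wording and a little more analysis work in software already named, with no new participants, visits or data. The price in assumptions is reliance on data being missing at random, which should be stated.

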**Methods/Design:**

A 3-arm RCT with waitlist control design will be used in this study. Two hundred and one elderly participants with very mild to mild dementia will be screened and randomized into the following groups: (i) dance movement based intervention, (ii) stretching and exercise intervention and (iii) no intervention waitlist-control group. The two intervention groups will receive a 1-h intervention, twice a week, for 12 weeks. The participants will be assessed four times over the course of 12 months: baseline before randomization, post-intervention (3 months), 6 months from baseline and 12 months from baseline. The primary outcomes will be compared between assessment points and between groups on neuropsychiatric symptoms, psychosocial well-being and cognitive and daily functioning. Secondary outcomes will assess the changes in salivary cortisol levels and their relationships with the primary outcome measures.

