### Research objectives

The primary objective of the proposed study is to explore the effects of a dance movement based intervention on dementia-related indicators such as neuropsychiatric symptoms (behavior, psychosis, ,apathy), psychosocial well-being (depression, loneliness and current affective state), physiological stress (indicated by cortisol), cognitive functioning (executive function, episodic memory, visuospatial construction) and daily functioning. The secondary objectives of this study are to explore the proposed intervention’s effect on dementia prognoses and examine how cortisol levels relate to neuropsychiatric, psychosocial, cognitive and functional measures in early dementia. Through these objectives we aim to provide insight into possible mechanisms of change and interactions among the aforesaid variables after dance-movement intervention.

We hypothesize that upon completion of the dance-movement intervention, elderly dementia patients will experience a greater delay in the progression of dementia severity compared with the exercise and control groups. Furthermore, those who participate in the dance-movement intervention should experience greater resilience against dementia-related decline, compared with the exercise and control groups. We expect to find an association between cortisol levels and neuropsychiatric, cognitive and daily functioning, in addition to psychosocial measures.

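### Eight unranked primary instruments and two comparators share one per-test p < .05 criterion, so the error of the efficacy conclusion is not controlled, and the outcome tiers conflict

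*Protocol article*

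**What the plan says.** **Primary outcomes.** The Methods/Design part of the abstract states: "The primary outcomes will be compared between assessment points and between groups on neuropsychiatric symptoms, psychosocial well-being and cognitive and daily functioning". The Measurements section covers these four domains with eight instruments:

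- neuropsychiatric: NPI
- psychosocial: ac-GDS, c-JFLS, VAMS
- cognitive: Digit Span, Fuld Object Memory Evaluation, Trail Making Test
- daily functioning: IADL-hk

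The article names no lead outcome, order, composite or primary time point.

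**Analysis.** The section on exploring efficacy compares dance with exercise and with waitlist by repeated measures ANOVA over the four assessments: "The data analysis procedures will be conducted using SPSS and MPlus software with criteria for levels of significance set at" p < .05.

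**Sample size.** It rests on "multiple regression modeling with a medium effect size (f2) of 0.15, at 0.8 power and a significance level of 0.05", that is, on one model tested once at 0.05.

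**Tiers.** The primary objective includes "physiological stress (indicated by cortisol", closing bracket omitted, among its indicators. The abstract says "Secondary outcomes will assess the changes in salivary cortisol levels". The first hypothesis under Research objectives is that "elderly dementia patients will experience a greater delay in the progression of dementia severity", yet the effect on prognosis is a secondary objective in the same section and appears in neither outcome tier of the abstract.

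**The concern.** A per-test level of .05 limits the error of one test. It does not limit the error of a conclusion that could rest on any of eight instruments against either of two comparators. The article makes claims of that kind: the abstract's Discussion expects the trial to supply strong evidence of efficacy, and the main Discussion speaks of confirming earlier findings and supporting effectiveness.

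If one instrument out of eight favours dance, nothing in the text says whether the trial has succeeded. Nor could a reader tell a planned success from a selected one. The tier conflict makes this worse, because cortisol or dementia progression could be moved up or down according to the result and still match some sentence of the protocol.

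**Working it through.** **1. The plan's own figure.** Inputs from Sample size determination: f² = 0.15, power 0.80, alpha 0.05, 131 evaluable, about 35 % attrition, 201 recruited. The number of predictors is not given; the text says only "The experimental, clinical and demographic variables anticipated to affect the intervention outcomes were included in the model". Using the overall F test of a regression with noncentrality f² × N, 12, 13 and 14 predictors need N = 127, 131 and 135. So 131 is reproduced with 13 predictors (assumed), with power 0.802. Inflation gives 131 / 0.65 = 201.5, which agrees with 201 up to rounding. The calculation provides for one test at 0.05.

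**2. Number of outcomes.** NPI 1 + psychosocial 3 + cognitive 3 + IADL 1 = 8 instruments. I take one score per instrument.

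**3. Simple case by formula.** Assumptions: no true effects, two-sided tests at .05 (the article does not state sidedness), one test time, independent outcomes. A false result in favour of dance has probability 0.025 per test. With one contrast:

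1 − 0.975⁸ = 0.183

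With both contrasts, the dance arm is shared. By simulation, the chance that either contrast falsely favours dance on one outcome is 0.045. Over eight independent outcomes:

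1 − (1 − 0.0451)⁸ = 0.309

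**4. Correlated outcomes.** The article gives no correlations, so I show 0 to 0.8. Simulation: 200,000 runs, three equal arms, equally correlated outcomes, large-sample z tests, z = (dance − comparator) / √2 in units of the standard error of one arm mean, favourable if z > 1.96. The gated row also requires the three-arm chi-square on 2 df to exceed 5.99 for that outcome.

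| Eight outcomes, at least one false result | ρ = 0 | 0.3 | 0.5 | 0.8 |
|---|---|---|---|---|
| Favours dance, one contrast | 18.3 % | 15.2 % | 12.5 % | 8.0 % |
| Favours dance, either contrast | 31.0 % | 25.5 % | 20.9 % | 13.7 % |
| Same, only after a significant three-arm test | 15.5 % | 13.3 % | 11.2 % | 7.1 % |
| Favours dance on both contrasts, same outcome | 3.6 % | 3.3 % | 3.0 % | 1.9 % |

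A single two-sided test has a false result in favour of dance 2.5 % of the time. Each of the first three rows lies above 5 %. Only the last does not, and it needs a rule that the article does not contain.

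**5. What the remedies do.** One designated outcome with the contrasts in fixed order holds the two-sided error at 0.05 and leaves the 131 of step 1 as it is. Bonferroni over eight instruments would use 0.05 / 8 = 0.00625. With the same assumed 13-predictor model, power at N = 131 falls from 0.80 to 0.52, and 80 % power needs 188 evaluable, or 188 / 0.65 = 289.2, so 290 recruited.

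**6. Tiers side by side.** Cortisol is primary under Research objectives and secondary in the abstract. Progression is the first hypothesis, a secondary objective, and absent from the abstract's outcomes. Under Measurements, CDR is listed as a screening instrument, rated before randomization and at 12 months only.

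**The case against.** **The article is condensed, and a separate analysis plan may adjust for multiplicity.** This stands as far as it goes: a missing adjustment procedure is not the point here. But the protocol does answer which outcomes are primary, by naming four whole domains, and it does set the criterion. The tier conflict lies within the article itself.

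**The study is exploratory.** The primary objective and the analysis heading do speak of exploring. The directional hypotheses and the efficacy claims in the abstract and Discussion do not fit that label.

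**Dance must beat both comparators.** The hypotheses name the exercise and control groups together. If superiority to both on the same outcome were required, the error would be about 2 to 4 %. No such decision rule is written.

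**The ANOVA is one model over all visits.** This is right, and the article does not say how contrasts follow from it. The gated row is the more lenient reading, and it still exceeds 5 %.

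A reader might also go further than the text allows:

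- *That at least 17 scores are tested.* Counting eight VAMS moods, two Fuld scores and two Trail Making parts gives 17. But the article does not say which scores are analysed, and one Fuld score would make it 16. More scores would raise the error; by how much cannot be fixed.
- *That the error is 41 to 53 % for eight instruments.* That is the two-sided figure for both contrasts (correlation 0.5 to 0). It also counts false results against dance, which would not support an efficacy claim.
- *That three follow-up visits raise it further.* This assumes separate tests at each visit, whereas the ANOVA treats time as a factor.
- *That a trial-wide 5 % was promised.* It was not; "with criteria for levels of significance set at" p < .05 is a per-test statement.

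**Conclusion.** The point holds in this form. The protocol fixes eight unranked primary instruments and two comparators under one per-test criterion, and presents the result as evidence of efficacy. The criterion does not control the error of that conclusion. The chance of at least one false result in favour of dance is about 21 to 31 % (14 % at correlation 0.8) if either contrast may count, and about 11 to 16 % (7 % at 0.8) if contrasts are gated by a three-arm test.

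These figures assume no true effects, one score per instrument, one test time, two-sided tests, equal arms and equal correlations among outcomes. The correlations and the gate are not in the article. Separately, and without any arithmetic, the tiers for cortisol and for dementia progression are inconsistent and need to be reconciled.

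**What to change.** Before results are seen:

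1. Name one primary outcome and one primary time point at which it is measured. If progression on the CDR is chosen, that can only be 12 months, because the CDR is rated only before randomization and then.
2. On that outcome, test the two dance contrasts in a stated fixed order, each at .05 and the second only if the first succeeds. Alternatively, state that dance must beat both comparators.
3. Make all other measures secondary under one multiplicity adjustment across the whole set, or label them exploratory. Adjusting separately within each domain would leave the error across domains uncontrolled.
4. Put cortisol and CDR progression each in one tier, the same in abstract, objectives and analysis.

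The cost is wording in the protocol and registry entry, and fewer outcomes that can be claimed as confirmatory. The test level stays at 0.05, so the stated 131 evaluable and 201 recruited need not change. The rule of beating both comparators is the stricter choice and has less power at the same sample size than either contrast alone.
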